### Intervention

IPS coaching as the manualized, evidenced based form of Supported Employment (SE) for people with mental illness focusses on an individualized, rapid search for competitive employment according to the client’s needs and preferences [24]. In addition to the emphasis on an individualized job support, the integration of accompanying mental health and employment services also plays a major role. The Supported Education Approach (SEA) can be considered equivalent to SE, but focusses more on the career start. This means, Supported Education aims at enabling the (mentally burdened) young individuals to (a) set and achieve an educational goal (e.g., training certificate or degree), (b) improve educational competencies (literacy, study skills, time management), (c) navigate the educational environment (e.g., applications, financial assistance), and (d) improve attitude and motivation toward completing educational goals [17]. An overarching goal is to support the transition to sustainable employment or training relationship [17].

As both support approaches take into account the interrelationships of health stabilization, coping with everyday life, social environment as well as professional development, they represent holistic concepts of coaching [25]. In line with this, the StAB intervention will also conceptualize the IPS coaching intervention as a kind of “lifeworld coaching”, including a wide variety of topics, depending on the support desired or needed by the participant. Additionally, a peer-counselling component will be implemented as part of the intervention program. In general, the StAB programs concept of supported education and employment is intended to overcome various individual challenges, such as 1) solving individual problems in different areas of life, 2) exploring one’s own strengths and interests and developing a professional goal, 3) providing information needed by the participants for professional orientation and for taking up training or employment, 4) planning an application as well as supporting the search for a suitable job / training position, 5) preparing a good start at the apprenticeship or workplace, 6) discussing the arrangements of the participant’s training or job in the educational institutions and companies.

Besides the fragmented German social system (see above), the StAB program is not (yet) feasible under regular conditions of means-tested benefits in Germany, since vocational placement efforts are put on hold while the initial focus is on clarification of the (mental) health situation and the utilization of psychosocial treatment options, stabilization of the mental health situation and rehabilitation of working ability [26].

The participation in the StAB program offers improved opportunities to a sustainable entry into working life, it is voluntary and free of charge. The StAB program consists in assigning an IPS coach to each participant in order to provide individualised support for integration into labour market for the young adults and adolescents with mental illness. Thereby, a bridge to (re-)entry into training and work is to be built in parallel to the regular psychiatric treatment. The IPS coaching takes place exclusively in individual contacts. These contacts are coordinated in terms of timing and content according to the respective needs and the therapeutic treatment of the participants, focussing on the current situation by addressing stagnations in development, setbacks or crises. Moreover, as IPS coaching aims at strengthening the self-help potentials of the young people [27], the participants should play an active role in working out and achieving their goals. Therefore, IPS coaches in the StAB program do not just give advice but work out options together in order to have a positive effect on the participants’ own responsibility. This is an important aspect in order to evoke acceptance of the current health conditions and to focus on the resources of the adolescents and young adults. For this purpose, the coach is able to use various interventional approaches, aiming at sensitising the young people to perceive their own resources, to recognize critical situations for them and to reflect on their “usual” behaviour in order to try out new options for behaviour and action in a next step. If there are needs for support in the areas of housing, finances, authorities and agencies etc., the coach establishes contact with the relevant counselling centres, if this has not already been done by the responsible integration specialist at the job centre. The IPS coaches accompany the professional process with the psychiatric and social-pedagogical specialists and create helpful support and network structures. The integration planning takes place in coordination with the regular psychosocial treatment and integration system. Thus, the appropriate services from the regular social care system should also be considered as soon as vocational perspectives and the necessary implementation steps have been worked out. Treatment as usual introducing people to the labour market in Germany involves for example group-delivered vocational preparation or trial employment. In addition to the coaching process, the StAB program will be able to provide an “individual budget” to its participants, which can be used for individual rehabilitation or participation planning, if necessary. The individual budget is €50 for each participant per month, whereby the amount of the budget can vary and the total sum should be usable as a total budget.

In order to ensure a uniform standard of IPS coaching, the StAB coaching team will receive a modular training at the beginning and during the course of the project, including for instance motivational interviewing, basics of social law, and in particular the impact of mental illness on learning and working as well as the role of the coach with regard to participants and employer / training company. Although according to the IPS principles coaching is not time limited, there is a maximum duration of 30 months in our StAB program (due to the model character of this third-party funded study). However, during this period, participants receive comprehensive long-term support, even though they are already in employment or training.

Another component of the project is the establishment of a competence network with relevant actors from the fields of child and youth work, school, training, vocational participation and work as well as the psychosocial and psychiatric system. Through joint meetings and accompanying mixed-methods surveys of the competence network, needs for improvement will be identified, future strategies for the health and social care system will be developed, and joint cooperation agreements will have been ratified at the end.

### Assessments

The baseline assessment is intended to acquire data on different participant characteristics by means of a study-specific questionnaire, e.g. demographics, educational status, employment history, work situation, utilization of (mental) health services, and expectations towards study participation. Furthermore, several standardized questionnaires (see below) will be handed out to participants for self-completion, but they can receive support or clarification from the research team member at any time if they want to. In addition, a brief screening test of cognitive functioning will also be performed. The whole assessment procedure is expected to take approximately 75 to 90 minutes. It will be carried out by experienced, trained and supervised research team members that can support participants that have questions regarding the questionnaires. In addition to the baseline assessment (t0), there will be a short interim assessment after one year (t1) and a final assessment at the end of the intervention after a maximum of two and a half years (t2). The t2 assessment is announced early and repeatedly, and its implementation is closely coordinated with participants to achieve high participation rates, even among potential dropouts.

Moreover, in addition to the study assessments we plan to include standardized process data from the IPS coaches to obtain information on frequency, amount, and type of support across the course of the StAB program. An overview of all variables, instruments and outcome measures utilized in the study is given in Table 1.

**Table 1 pone.0271803.t001:** Diagnostic instruments and assessment schedule (the full names of the instruments are given in the text, see Measures).

		STUDY PERIOD		
		T0 (baseline assessment)	T1 (short interim assessment)	T2 (final assessment)
**TIMEPOINT** (months)		0	12	24
**ENROLMENT**				
Eligibility screen		✓		
Informed consent		✓		
**INTERVENTIONS**				
IPS-Coaching				
**ASSESSMENTS**				
Psychosocial participation and functioning	IMET	✓		✓
	WHODAS 2.0	✓	✓	✓
Mental health status	PHQ-9	✓	✓	✓
	SCL-K-9	✓	✓	✓
	L-1	✓	✓	✓
	SCIP	✓		✓
	AMS-R	✓	✓	✓
Self-esteem and self-efficacy	G-SISE	✓	✓	✓
	ASKU	✓	✓	✓
Psychosocial resources	Social contacts (LK-18)	✓	✓	✓
	BRS	✓		✓
	HLS-EU-Q16-GER	✓		✓
Study-specific questionnaires	Demographics, Professional biography, Work ability, Satisfaction with medical care, Work and employment prospects under corona conditions	✓	(✓) partially	✓

#### Measures

Table 1 shows the questionnaires as well as their measurement time point within the study.

*Psychosocial participation and functioning*. Developed by the WHO, the **WHODAS 2.0** (*World Health Organization Disability Assessment Schedule 2*.*0*) is an assessment instrument to measure health, functional impairment and disability across diseases, countries, and cultures in accordance with the International Classification of Functioning, Disability and Health (ICF) [28]. In our study we use the 12-item self-report version, that has been found to explain 81% of the variance of the most widespread 36-item version [28]. The 12-item WHODAS 2.0 presents high internal consistency (up to 0.96), reliability, sensivity to change as well as overall good correlations with other measures of disability [29].

The **IMET** (*Index zur Messung von Einschränkungen der Teilhabe*, German for: Index for the Assessment of Health Impairments [30]) was developed to assess participation and involvement for patients with different (chronic) diseases as described by the ICF. The extent of impairment in nine areas of everyday activities (e.g. family/household obligations, recreational and leisure activities) have to be indicated on an 11point scale from 0 = no impairment to 10 = no more activity possible. Cronbach’s alpha was .90 - .91. Convergent validity is supported by moderate to high correlations of the IMET total score with earning capacity and performance measures. Furthermore, normative data from a population-based survey allows classification of participation impairment [31].

*Mental health status*. For assessing the burden of psychopathology, the *9-item short version of the Symptom Checklist* (**SCL-K-9**) is used [32]. This short scale measures the subjectively perceived impairment by physical and psychological symptoms within a period of seven days. The SCL-K-9 exhibits satisfactory psychometric properties and its summed up total score is highly correlated with that of the original 90 items questionnaire (r = .93) [32], thus representing a Global Severity Index (GSI, [32]).

In order to assess the presence and severity of depressive symptoms, we chose the **PHQ-9**, which is based on the 9-item depression module from the *Patient Health Questionnaire* [33]. The PHQ-9 comprises the diagnostic criteria of major depression according to the *Diagnostic and Statistical Manual of Mental Disorders*, but also serves as a severity measure since each of the 9 items can be scored from 0 (not at all) to 3 (nearly every day). As a well-established depression screener, the PHQ-9 has been found to have good psychometric characteristics as well as diagnostic validity and can be used to detect depression outcome and changes over time (e.g. [34]).

General life satisfaction will be measured using *The General Life Satisfaction Short Scale* (**L-1**) [35, 36]. This scale only consists of one item asking “All things considered, how satisfied are you with your life these days?” with 11 response categories ranging from “not satisfied at all” (0) to “completely satisfied” (10). As part of its development, the L-1 was evaluated with regard to its methodological quality in population samples from Germany and England [35, 36]. Although psychometric differences may appear when compared to multi-item equivalents [37], recent research findings support the use of single-item life satisfaction scales [38].

The *Screen for Cognitive Impairment in Psychiatry* (**SCIP**) is a brief and easy to administer screening tool for cognitive performance specifically developed for psychiatric populations [39]. It includes five subtests for assessing a) immediate and b) delayed verbal learning, c) working memory, d) verbal fluency, and d) processing speed. Moreover, the SCIP is available in different parallel forms to facilitate a prospective assessment of the cognitive status. The applicability and methodological criteria of the SCIP have been verified in different countries [40–42] and recent study results with the German version [43] showed that it is a valid and reliable cognitive screening tool.

*Self-esteem and self-efficacy*. The global self-esteem level will be measured using the *German version of the Single-Item Self-Esteem Scale* (**G-SISE**) [44]. The G-SISE asked participants to respond to the statement “Please indicate to what extent the following statement applies to you: I have high self-esteem.” on a 5-point Likert scale (1 = “not at all true of me” to 5 = “very true of me”). Studies have not only identified convergent correlations of around r = .75 between the SISE and the well-known 10-item Rosenberg Self-Esteem scale, but also supported the reliability and validity of the ultrashort scale [44, 45].

The GSE-3 (*General Self-Efficacy Short Scale–3*) consists of three items and is used to economically measure subjective competence expectations to be able to deal with difficulties and obstacles in daily life [46]. The short scale has a unidimensional structure, reliability varies between .73 and .92, and scalar measurement invariance holds across different European countries [44, 45]. In the present study, the original German-language scale of the GSE-3, called “Allgemeine Selbstwirksamkeits Kurzskala” (**ASKU**), will be applied [47].

We use the *revised 10-item version of the Achievement Motives Scale* (**AMS-R**) to assess hope of success and fear of failure [48]. The AMS-R was adjusted with regard to the factorial structure and provides adequate reliability as well as criterion-related validity with respect to typical achievement-related behaviour. Research studies have indicated that motivational variables seem to relate to psychosocial and vocational functioning in psychiatric patients [49, 50].

*Psychosocial resources*. Measuring the ability to recover from stress, the German adaptation of the *Brief Resilience Scale* (**BRS**) [51] consists of six items (e.g. “I tend to bounce back quickly after hard times”), that have to be rated on a five-point Likert scale ranging from 1 = strongly disagree to 5 = strongly agree. Results from studies with large (representative) samples yielded evidence for the reliability and validity of the German BRS and also provided population-based norms [51, 52].

The German version of the Rasch scaled short form of the *European Health Literacy Questionnaire* with 16 items (**HLS-EU-Q16**) captures different dimensions of (general) health literacy skills (finding, understanding, judging and applying health information) in the areas of disease prevention, health promotion and health care [53]. Respondents are asked to rate on a 4-point scale how easy they think each health literacy task or activity is (very easy—very difficult). For both the German (e.g. Cronbach’s α = 0.90) and further European versions, the HLS-EU-Q16 showed good results for internal consistency and other psychometric features [54, 55]. Following a recent approach [56], we additionally included another item from the original long form of the HLS-EU-Q47 [57] to compose a brief four-item Mental Health Literacy subscale.

In order to capture the involvement in social network structures with supportive relationships and close contacts, the “**social contacts**” subscale from the German Life Skills questionnaire (Lebenskompetenz-Fragebogen, LK-18) [42] will be used. It comprises three items (e.g. “I experience interpersonal support in life”) to be answered on a 5-point-Likert Scale. The subscale’s internal consistency was Cronbach’s α = .75.

*Further measures and questions*. As we want to assess participants’ **subjective work ability**, we therefore use several single items from different assessment tools (1) Würzburger Screening [58], 2) Short Screening Instrument of Need for Occupation Related Treatment in Medical Rehabilitation (SIBAR) [59], 3) Indicators of rehabilitation status, version 3 (IRES-3) [60].

In addition to the aforementioned measurement instruments, we will collect data on **various participant characteristics** across the study period using study-specific and self-constructed questionnaires. Here, the main focus is on professional and educational development, utilization of psychosocial support services as well as participation in and satisfaction with the program. Moreover, we also plan to include standardized process data from the IPS coaching team to obtain information on frequency, amount, and type of support across the course of the program. Additionally, the subjectively perceived impact of the corona pandemic on the education and employment situation of the participants will be obtained. For this purpose, questions from a recent short survey on vocational perspectives for people with mental illness under corona conditions will be used [61].

#### Data analyses

Before data analysis, the data set will be inspected with regard to inconsistencies and missing values. Missing data will be addressed by applying linear mixed models, if appropriate. We will perform a dropout analysis to check for differences between program completers and non-completers with regard to main demographic, psychosocial, and work-related variables. Besides descriptive baseline data analysis, we will primarily analyse changes in the main outcome measures from baseline to final assessment (after up to a maximum of 2.5 years). Theses analyses on the study outcome measures will be performed as intention-to-treat, supplemented by a “per-protocol”-analysis including all individuals who have completed the StAB program without dropping out. Of course, a repeated-measures approach is used if indicated. Program effects on outcome measures will be explored by taking into account relevant covariates, like key baseline variables, changes in some measures within the first year (see above) or program specific variations, e.g. number and total duration of coaching sessions. Program feasibility and acceptance among the participating adolescents and young adults with mental health difficulties will be evaluated using process documentation data as well as subjective ratings in the final assessment.

The statistical analysis of the data will be done using the software package IBM SPSS Statistics Version 25 and the level of statistical significance will be set to p < .05.

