### Sample size

With regard to the central outcome parameters, an improvement in the questionnaire results (e.g. psychosocial participation and functioning, quality of life, self-efficacy) between the initial and final assessment is expected over the two-year StAB intervention period. Thus, considering A) a paired t-test for dependent samples as the statistical analysis method, B) a small to medium effect size (d = 0.4), C) an α-(error) level of 0.05, and D) a β-level of 0.2 (or a power of 0.8), the a priori case number estimation using the programme G*Power 3.1 [23] resulted in a required sample size of n = 52 persons. Assuming a dropout rate of at least 30% during the 24 months period after recruitment, at least 75 people should be included into the study.

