Nevertheless, the implementation and evaluation of the presented study is also associated with some challenges and limitations. For instance, we will face possible challenges with regard to the recruitment of the targeted group of people. Emerging adults with mental illnesses already face many difficulties to cope with a particularly vulnerable phase of life. It has been shown that they may not actively seek professional help themselves (see [73]) due to stigmatization and shame as well as a preference for self-reliance [74] and that they tend to disengage from ongoing intervention services by virtue of adverse vocational trends (e.g. [75]). Thus, accessibility to the program and reachability to these young people across the study period may be potentially difficult. We therefore expect a 30% dropout rate, in line with other IPS studies [76] and even slightly higher than comparable vocational programs for mentally burdened young adults [77].

Another challenge to both study initiation and implementation may be the ongoing (or re-emerging) restrictions due to the Corona pandemic. In addition to constraints on the conduct of research projects (e.g. [78]), the longer-term work-related perspectives and participation opportunities of people with mental illness seem to have been additionally worsened under Corona conditions [61]. Moreover, of course, many young individuals have reported being highly burdened by the pandemic [79] and experiencing more mental health problems [80].

A methodological limitation of the present study is the use of a single group pre-post design, because we will not be able to control for potential confounders. In order to have something similar to a control group, we will compare the data from participants of the IPS coaching with data of the federal average or data of standard labour market policy measures. Wherever possible, not only intra-group changes will be analysed, but also comparisons with published norms of the test procedures as well as results of other studies will be used. Nevertheless, a RCT study design should be a future approach.

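### Mixed models are the only stated handling of missing final scores, while the protocol's own account of dropout gives reason to doubt the assumption they need; the pre-post change is liable to be biased towards benefit

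*Protocol article*

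**What the plan says.** The Data analyses section states one statistical method for missing outcomes: "Missing data will be addressed by applying linear mixed models, if appropriate". The model terms are not given. The main contrast is the pre-post change: "we will primarily analyse changes in the main outcome measures from baseline to final assessment". The analyses are to be "performed as intention-to-treat, supplemented by a “per-protocol”-analysis including all individuals who have completed the StAB program without dropping out". A comparison of leavers and stayers is also planned: "We will perform a dropout analysis to check for differences between program completers and non-completers", on demographic, psychosocial and work-related variables.

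The Discussion says of these young people that "they tend to disengage from ongoing intervention services by virtue of adverse vocational trends". It goes on to expect difficulty in reaching them during the study and concludes: "We therefore expect a 30% dropout rate, in line with other IPS studies". The Sample size section uses the same rate: "Assuming a dropout rate of at least 30% during the 24 months period after recruitment, at least 75 people should be included into the study".

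Three other places matter. Table 1 schedules WHODAS 2.0 at T0, T1 and T2, but IMET only at T0 and T2. The Assessments section plans early, repeated and coordinated efforts to obtain the final assessment, including from people who might drop out. Study design and setting states that there is no control group.

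**The concern.** A likelihood-based mixed model gives an unbiased mean change if the chance of a missing final score depends only on data in the model (missing at random). The Discussion names a driver of disengagement, an adverse vocational course, that develops between visits a year or more apart. The stated method does not say that this course enters the model.

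The driver plausibly bears on the primary outcomes. The Objectives make psychosocial participation and functioning primary, and the Measures section reports that IMET correlates moderately to highly with earning capacity and performance. If people leave because their vocational course is poor, their unseen final scores may be worse than their earlier scores predict.

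A participant without T2 contributes only a baseline score for IMET. The model then in effect assigns that person the stayers' change, adjusted for baseline. The same holds for WHODAS in people who leave before T1. In a single-arm study the pre-post change is the whole effect estimate, so no comparison group shares such a bias and cancels it.

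**Working it through.** **The plan's own figures.** A two-sided paired t-test with d = 0.4 and alpha 0.05 reaches 80% power at n = 52 (exact power 0.808). Inflating for 30% dropout gives 52 / 0.7 = 74.3, hence 75. Both figures reproduce. They also show that the protocol counts this dropout as lost outcome data.

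**Assumptions (not in the document).** Each score has SD 1, and visits correlate at 0.5. The SD of change is then √(2 × (1 − 0.5)) = 1, so 0.40 SD equals the plan's d = 0.4. Improvement is counted as positive, and 30% lack T2.

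**A. Fixed change in leavers.** Stayers improve by 0.40, half of the leavers also lack T1, T1 change is half of T2 change, and baselines are equal.

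- Truth = 0.7 × 0.40 + 0.3 × (leaver change).
- Two-visit model (IMET): leavers add only baseline, so the estimate is the stayers' 0.40.
- Three-visit model (WHODAS): the T2-on-T1 coefficient, given T0, is 0.5 / 1.5 = 1/3. The T1 mean is (0.70 × 0.20 + 0.15 × leaver T1 change) / 0.85. The estimate is 0.40 + (T1 mean − 0.20) / 3.

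| Leaver change | Truth | T1 mean | Three-visit | Two-visit |
|---|---|---|---|---|
| 0.40 | 0.40 | 0.200 | 0.40 | 0.40 |
| 0.20 | 0.34 | 0.182 | 0.39 | 0.40 |
| 0 | 0.28 | 0.165 | 0.39 | 0.40 |
| −0.20 | 0.22 | 0.147 | 0.38 | 0.40 |

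Simulation of the no-change and worsening cases gives the same to within 0.01.

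**B. Dropout driven by a mechanism.** The true change is 0.40 and the log-odds of a missing T2 rise by 1 per unit worsening of the driver. Everyone has T1 in the three-visit model. The fit is by maximum likelihood with unstructured covariance, on 100,000 simulated people.

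| Driver of dropout | Three-visit | Two-visit |
|---|---|---|
| Observed T1 score | 0.40 | 0.47 |
| Unmodelled vocational course, correlation 0.3 with score change | 0.45 | 0.46 |
| Unmodelled vocational course, correlation 0.5 with score change | 0.49 | 0.50 |
| The T2 score itself | 0.575 | 0.595 |

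For the vocational driver the overstatement is 0.05 to 0.10 SD, that is 0.05 / 0.40 = 12.5% to 0.10 / 0.40 = 25%. The first row shows why IMET is more exposed: the T1 value that removes the bias for a three-visit scale does not exist for IMET.

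**Effect on the test.** With 52 evaluable people and no true change, a bias of 0.10 SD raises the chance of a significant result from 5% to about 11%, and a bias of 0.20 SD raises it to about 29%. Under the vocational driver with no true change, the simulated bias was 0.05 to 0.09 SD, so the chance stays below that 11%.

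**The case against.** The strongest reply is that the article states nothing false. Missing-data sensitivity analyses are often left to a full protocol or SAP, neither of which is shown, and the qualifier on the mixed model shows that the authors do not claim it suffices. The absence of a sensitivity analysis alone would indeed be a weak point. What remains is that the one method stated, followed under the protocol's own reasoning about dropout, is liable to err in one direction.

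Four stronger readings are tempting, and the documents do not support them.

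- **That the protocol contradicts missing at random.** The Discussion speaks of leaving services, citing other work, and takes its 30% from other programmes. It does not say that leavers' WHODAS or IMET scores fall below what earlier scores predict. It gives a reason for doubt, no more. Leaving the programme is also not the same as missing T2, and the efforts in the Assessments section may reduce the loss.
- **That the result will be biased.** If leavers change like stayers, or if dropout depends only on data in the model, there is no bias.
- **That no planned analysis could show the problem.** The dropout analysis includes work-related variables and can reveal selective dropout on what was observed. It cannot say how far the T2 change depends on it, or correct it. The per-protocol analysis selects completers further and does not help.
- **That the overstatement is about 40%.** That ratio, 0.40 / 0.28, only restates the assumption that leavers do not change.

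Vocational and educational development and coaching process data are already to be collected across the study, and the covariates listed for exploring effects include coaching amount. The material for a better model largely exists. The plan does not say that it will be used for missing scores.

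**Conclusion.** The point holds as a liability to bias. The stated handling of missing final scores relies on missing at random, and the protocol's account of who disengages gives a reason to doubt that. If poor vocational course goes with poor scores, the intention-to-treat change errs towards benefit. IMET is most exposed, then WHODAS for those who leave before T1.

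The illustrative size is 0.05 to 0.10 SD on a true 0.40 if dropout follows an unmodelled vocational course. It is 0.11 to 0.12 SD (0.39 to 0.40 against 0.28) if the 30% lost do not change at all, and zero if they change like stayers. All of these rest on assumed correlations and assumed outcomes in leavers, which the document does not give. The sample size of 52 evaluable and 75 recruited is unaffected.

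**What to change.** Keep the mixed model as the main analysis. For WHODAS and IMET, add to the Data analyses section:

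1. Multiple imputation of missing T2 scores, or an equivalent model, with the vocational and educational status and the coaching process data already collected as auxiliary variables. Where feasible, record vocational status at last contact in the coach record. This has to be collected prospectively and may not be recoverable later.
2. A delta-adjusted or tipping-point sensitivity analysis that includes the case of no improvement over T0 in people without T2.

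Report the main estimate alongside this range, and word conclusions about all participants to match it.

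The cost is a few lines of plan, a little analysis work and one record field. The headline estimate may become less favourable.
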